##### Ecological Momentary Assessment

Participants in both treatment groups will be prompted to complete ecological momentary assessments (EMAs) once per day during the initial 8 weeks, and once per week for the remainder of the study (4 months) via push notification. The method by which participants will complete EMAs will differ by treatment group, with QT participants completing EMAs online via REDCap and D-MAPS participants completing EMAs via the app. Using EMAs will allow us to examine the dynamic impacts of multiple psychological, social, and environmental factors during a quit attempt. Specifically, participants will be asked questions relating to their current smoking status, perceived stress level, smoking self-efficacy, motivation to quit smoking, and nicotine replacement therapy adherence [58].

##### Primary Outcome Measures

The primary outcome measures for demonstration project 2 will be the feasibility of the D-MAPS app, assessed via usability and acceptability. Specifically, usability will be assessed with the 10-item System Usability Scale [59], as well as through a single item assessing the percentage of participants who rate the app as “easy to use.” It will be deemed usable if at least 80% of participants score >70 (range 0-100) on the System Usability Scale and at least 80% of participants respond “yes” (dichotomous yes or no) to the app being “easy to use.” The acceptability of and satisfaction with the D-MAPS app will be assessed via the Client Satisfaction Questionnaire [60]. It will be deemed acceptable and satisfactory if (1) at least 80% of participants score >3 (range 1-4) on the Client Satisfaction Questionnaire, (2) at least 80% of participants report being mostly or very satisfied with the intervention, (3) at least 80% of participants respond “yes” to recommending the intervention to a friend to quit smoking, and (4) at least 80% of participants rate the quality of the intervention as good or excellent. Finally, various app engagement metrics will be measured (eg, video playback duration and frequency of app access).

##### Analytic Approach

This study is not designed or powered to test significant differences between our 2 conditions in demonstration project 2. However, we will describe cessation outcomes in both treatment conditions using 7-day point prevalence abstinence at each follow-up and calculate CIs. These data, combined with feasibility metrics, will be useful when designing a future, fully powered trial.

#### Demonstration 3: Data Collection and Processing via Machine Learning

##### Overview

Machine learning and deep learning, subfields of artificial intelligence, offer promising tools for identifying complex patterns in health-related data via computer algorithms in multiple domains, including cancer [61]. These methods are particularly well suited for analyzing data from diverse sources (eg, self-report, clinical assessments, wearable devices, and GPS) to generate predictive models of behavior. Despite this potential, machine and deep learning remain underutilized in mHealth interventions [62]. Therefore, the primary goal of demonstration project 3 is to evaluate the capacity of the mFLi platform to support the application of machine and deep learning methods for predicting key behavioral health outcomes (eg, smoking cessation and relapse). By integrating and analyzing data from the participants’ EHRs (eg, on diagnosis and treatment) and data collected from the 90 patients enrolled in demonstration projects 1 and 2 (split randomly; 70% of participants assigned to the training phase and 30% assigned to the validation and testing phases), this project aims to assess the feasibility of applying advanced analytic techniques to mHealth-collected data, thereby highlighting mFLi’s potential to shift traditional paradigms in behavioral research and support next-generation personalized interventions.

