##### Data Processing: Machine and Deep Learning

The application of machine and deep learning algorithms to mHealth can be enabled via two approaches: (1) cloud-based client server and (2) on-device app.

In cloud-based client server setup, the machine learning and deep learning algorithms are hosted in the cloud (server), with access to powerful computing resources (graphics processing units), and the data are sent from the mobile device (client) over the internet to the cloud. The main advantage in this case is that conventional and complex machine learning algorithms can be directly used. In such a scenario, the analysis can begin with conventional ensemble machine learning techniques, including random forests, which are robust to heterogeneous data types and have demonstrated strong performance in prior related studies [63-66]. The importance of different factors will be ranked using methods based on the Gini index (eg, permutation testing), and associated statistical metrics will be used to assess their significance. To address limitations inherent in traditional machine learning approaches, we will also explore deep learning models, which integrate feature extraction directly into the predictive modeling process [67]. These models are particularly well suited for large, high-dimensional datasets. To enhance model interpretability, we will use techniques such as Shapley Additive Explanations values and interpretability maps, allowing us to rank order key predictors contributing to model outcomes [68-70]. If sample size limits the performance of deep learning models, we will use hybrid models that combine both conventional machine learning and deep learning techniques [71]. The main disadvantages in this case are latency and privacy concerns.

In on-device app setup, the machine and deep learning algorithms can run directly on the mobile device. Typically, the algorithms are developed offline as described earlier (training mode), then deployed on the device (inference mode). The inference mode is less computationally demanding and can benefit from existing frameworks such as Core ML (Apple Inc) on Apple iOS and TensorFlow Lite (Google LLC) on Android systems. This approach provides advantages such as real-time performance, offline functionality, and improved privacy by maintaining the data secured on the device. This approach will be favored in our design.

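### A single 70/30 split of 90 participants leaves 27 for validation and testing together, so demonstration 3 could say little about predictive performance; participant-level nested cross-validation would use the data better

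*Protocol article*

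**What the plan says.** The Overview of demonstration 3 says the "primary goal of demonstration project 3 is to evaluate the capacity of the mFLi platform" to support machine and deep learning, and adds that "this project aims to assess the feasibility of applying advanced analytic techniques to mHealth-collected data". The outcomes are given by example: "predicting key behavioral health outcomes (eg, smoking cessation and relapse"). The material is EHR data together with "data collected from the 90 patients enrolled in demonstration projects 1 and 2", and these participants are "split randomly; 70% of participants assigned to the training phase and 30% assigned to the validation and testing phases". The article does not say how the 30% is divided between its two phases, which performance measure will be used, or what precision is wanted.

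The section on data processing starts with random forests, then explores deep learning, and adds a fallback: "If sample size limits the performance of deep learning models, we will use hybrid models". Predictors are to be ranked by Gini-based methods and by Shapley values. On-device use is favoured; in that setup "the algorithms are developed offline as described earlier (training mode), then deployed on the device (inference mode").

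**The concern.** The split is a design choice that the article fixes, not a detail left open. It takes 27 of 90 people out of model building, yet the 27 have to serve both validation and testing. If they are divided, the test set is very small. If they are not, the people used to choose among forest, deep and hybrid models also judge the chosen one, and the estimate is optimistic. The one remark on sample size responds by changing the model type; it adds a candidate model and leaves the evaluation set as it is.

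At stake is any statement about how well cessation or relapse can be predicted, or which predictors matter. Such statements would naturally be carried into the design of a later trial or into an on-device model.

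**Working it through.** **Inputs from the article.** 3000 prescreened, 10% smokers, 30% enrolled; 70/30 split; one EMA prompt a day for 8 weeks, then one a week for 4 months.

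**Assumed, because the article gives no figure.** AUC 0.75; events in 10% to 40% of participants; no dropout.

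**1. Sample.** 3000 × 0.10 = 300 and 300 × 0.30 = 90, which reproduces the planned enrolment. Then 0.70 × 90 = 63 and 0.30 × 90 = 27; half of 27 is 13.5.

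**2. Precision of the AUC (Hanley-McNeil).** With A the AUC, n₁ events and n₀ non-events:

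SE² = [A(1−A) + (n₁−1)(Q₁−A²) + (n₀−1)(Q₂−A²)] / (n₁n₀), with Q₁ = A/(2−A) and Q₂ = 2A²/(1+A).

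At A = 0.75, Q₁ = 0.600, Q₂ = 0.643 and A² = 0.5625. For n = 27 and 20% events, n₁ = 5.4 and n₀ = 21.6, so SE² = (0.1875 + 0.165 + 1.655)/116.64 = 0.0172, SE = 0.131, and the half-width is 1.96 × 0.131 = 0.26.

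| Events | n = 13.5 | n = 27 | n = 90* |
|---|---|---|---|
| 10% | 0.51 | 0.35 | 0.19 |
| 20% | 0.37 | 0.26 | 0.14 |
| 30% | 0.31 | 0.22 | 0.12 |
| 40% | 0.29 | 0.20 | 0.11 |

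*Treats all 90 as independent test cases. Cross-validated predictions are not independent, so this column is a best case and not what cross-validation delivers.

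With 27 tested, the normal-approximation interval is about 0.49 to 1.00 at 20% events, which includes chance (0.50), and about 0.55 to 0.95 at 40%, which does not.

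**3. Other views of the same numbers.** At 20% events, a 14-person test set has a 20% chance of holding one event or none (binomial). An observed accuracy of 70% has a Wilson 95% interval of 44% to 87% with 14, 51% to 84% with 27, and 60% to 79% with 90.

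**4. What nested cross-validation gains.** The formula ratio of 90 to 27 is about 0.54 (√(27/90) = 0.55), but it rests on the independence noted above. So the procedure itself was simulated: 90 participants, 20 predictors of which 5 carry signal, ridge logistic regression, 20% or 30% events, two signal strengths, about 400 runs each. The measure is the root mean squared error (RMSE) of estimated against true performance.

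| Events, signal | AUC RMSE, 14 tested | 27 tested (tuned within training) | Nested 5-fold, all 90 | Ratio to 14 | Ratio to 27 |
|---|---|---|---|---|---|
| 20%, weaker | 0.202 | 0.143 | 0.103 | 0.51 | 0.72 |
| 20%, stronger | 0.181 | 0.131 | 0.087 | 0.48 | 0.67 |
| 30%, weaker | 0.174 | 0.126 | 0.087 | 0.50 | 0.69 |
| 30%, stronger | 0.170 | 0.106 | 0.075 | 0.44 | 0.71 |

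The error is about half that of a 14-person test set, and about 30% below that of a 27-person one. For accuracy the ratio to 27 is 0.57 to 0.63.

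**5. Momentary outcomes.** 8 × 7 = 56 daily prompts plus about 17 weekly ones is about 73 per person, so 27 people give up to 27 × 73 = 1,971. These are clustered within person. The effective size exceeds 27 by an amount that the article does not allow one to compute.

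**The case against.** The strongest reply is that demonstration 3 is a feasibility exercise. It sets no performance threshold and makes no claim to a validated model, so an imprecise AUC does not make it fail. That stands, and it limits the point to what may be said about performance and predictors.

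A second reply also stands. A single hold-out keeps an untouched test set for the one model that might go onto the device. Nested cross-validation evaluates a modelling procedure and gives that up, so the change is not free.

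Some stronger readings are tempting, but the documents do not carry them:

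- A reader might infer that cross-validation halves the uncertainty relative to all 27. That follows only from the independence formula; the simulated gain is nearer 30% for AUC. Halving holds against a test set of 13 to 14.
- A reader might infer that the same 27 people both choose and judge the model. The article names two phases and does not say how they share the 27; choosing on one part and testing on the other is the more ordinary reading.
- A reader might infer that a good model could never be told from a useless one. At 40% events and an AUC of 0.75, the interval with 27 excludes chance.
- A reader might take the statement that predictors are "ranked using methods based on the Gini index (eg, permutation testing") as an error. A permutation test applied to a Gini statistic is coherent, and the article also plans significance metrics and Shapley values.
- Stratification of the split is not mentioned, but a condensed article may leave that to the full plan.

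**Conclusion.** The point holds as one about precision and efficient use of 90 participants. For an outcome measured once per person, the planned split gives a 95% half-width for the AUC of about 0.20 to 0.35 with 27 tested and 0.29 to 0.51 with 13 to 14. These figures rest on an assumed AUC of 0.75, 10% to 40% events and no dropout; any dropout would widen them. For momentary outcomes the loss is smaller by an unknown amount. Demonstration 3 can still show that the platform supports these methods. It could say little about how well they predict.

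The gain from cross-validation was simulated for one model class without repetition of the folds. Against 27 it is best quoted cautiously, as about 25% to 30% for AUC.

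**What to change.** Replace the single split with repeated nested cross-validation on all participants:

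- Keep each participant whole within a fold, which is essential if EMA or wearable records are the unit of prediction.
- Do all tuning, and the choice among forest, deep and hybrid models, in the inner folds.
- Report performance with intervals and label it exploratory.
- For any on-device model, refit the chosen procedure on all data, and state that the refitted model has had no untouched test.

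No extra participants or data are needed. The article places analysis after data collection, expected to end in May 2027, so the plan can still be changed. The costs are more computing, intervals that are harder to obtain because folds share data, and no locked hold-out for the final model. If a hold-out is kept for that last reason, the plan should say how the 27 are divided and give the precision to expect.

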##### Data Processing: Machine and Deep Learning

The application of machine and deep learning algorithms to mHealth can be enabled via two approaches: (1) cloud-based client server and (2) on-device app.

In cloud-based client server setup, the machine learning and deep learning algorithms are hosted in the cloud (server), with access to powerful computing resources (graphics processing units), and the data are sent from the mobile device (client) over the internet to the cloud. The main advantage in this case is that conventional and complex machine learning algorithms can be directly used. In such a scenario, the analysis can begin with conventional ensemble machine learning techniques, including random forests, which are robust to heterogeneous data types and have demonstrated strong performance in prior related studies [63-66]. The importance of different factors will be ranked using methods based on the Gini index (eg, permutation testing), and associated statistical metrics will be used to assess their significance. To address limitations inherent in traditional machine learning approaches, we will also explore deep learning models, which integrate feature extraction directly into the predictive modeling process [67]. These models are particularly well suited for large, high-dimensional datasets. To enhance model interpretability, we will use techniques such as Shapley Additive Explanations values and interpretability maps, allowing us to rank order key predictors contributing to model outcomes [68-70]. If sample size limits the performance of deep learning models, we will use hybrid models that combine both conventional machine learning and deep learning techniques [71]. The main disadvantages in this case are latency and privacy concerns.

In on-device app setup, the machine and deep learning algorithms can run directly on the mobile device. Typically, the algorithms are developed offline as described earlier (training mode), then deployed on the device (inference mode). The inference mode is less computationally demanding and can benefit from existing frameworks such as Core ML (Apple Inc) on Apple iOS and TensorFlow Lite (Google LLC) on Android systems. This approach provides advantages such as real-time performance, offline functionality, and improved privacy by maintaining the data secured on the device. This approach will be favored in our design.

##### Handling Missing Data

We will make every effort to keep missing data at a minimum. We will compare the characteristics of responders and participants who dropped out of the study. Additionally, several imputation strategies (eg, last value carried forward, regression approaches, and missing equals smoking) will be used as sensitivity tests.

## Results

This study was funded by the Florida Department of Health (23K01) in May 2023 and approved by the institutional review boards at the University of Miami (approved April 2025), University of Florida (approved October 2025), and Moffitt Cancer Center (approved February 2024). Recruitment for the study began in March 2025 and is ongoing, with enrollment expected to be finalized in November 2026. As of January 2026, 41% (37/90) of the target sample have consented and been enrolled into the study. Participants are followed for 6-months after baseline; as of January 2026, 21% (19/90) have completed the 6-month follow-up assessment. Data collection is expected to be completed once the final participant completes the 6-month assessment (expected May 2027). Following data collection, data will be analyzed and findings will be disseminated.

## Discussion

### Expected Outcomes and Potential Impact

The purpose of this study is to develop mFLi and to evaluate the feasibility of the platform via 3 demonstration projects. The results from this study will address existing challenges related to developing evidence-based mHealth treatments (eg, complicated, time-intensive, and resource-intensive) by supporting, streamlining, and reducing the costs of developing and disseminating digital interventions. Specifically, results will be critical for informing future mFLi infrastructure changes, including, but not limited to, the following areas: randomization, e-consent, EMA, automated delivery of financial compensation, notifications, and delivery of content. We also anticipate that results from this demonstration project will provide support for a subsequent RCT and will inform the need for additional modifications to the app prior to efficacy testing. Thus, mFLi may enhance the efficacy of digital health interventions, health outcomes, and health care delivery.

### Dissemination Plan

The findings from this study will be disseminated through peer-reviewed publications, conference presentations, and meetings with relevant stakeholders. We will leverage existing relationships with our advisory boards (Scientific Advisory Board and Community Advisory Board) and funders to identify key stakeholders who may benefit from or contribute to the dissemination of findings from this and subsequent studies. These partnerships will also inform ongoing refinement and development of mFLi. In collaboration with stakeholders, we will also explore opportunities for future funding and resources to support broader implementation and dissemination efforts.

### Clinical Relevance and Potential Strengths

The infrastructure has several unique strengths, including (1) reducing the burden on researchers desiring to develop mHealth interventions and on diverse individuals and populations seeking personalized, cost-effective, and evidence-based treatment; (2) enabling multi-device integration (ie, wearable devices) through a flexible architecture that allows for the collection, integration, and analysis of multiple data sources; (3) embedding robust security, regulatory, and compliance guardrails for users across internal and external institutions; (4) featuring flexible design capabilities allowing future apps to leverage existing features or develop new functionality as technology and needs evolve; and (5) involving multiple partners including 3 organizations with different structures.

### Potential Limitations

The proposed infrastructure also has anticipated limitations that should be mentioned, including requiring all users to own a smartphone with an operating system compatible with the project app (Apple iOS or Google Android operating systems); however, smartphone ownership is now nearly ubiquitous (91% of US adults own a smartphone [13]) and iOS and Android combined encompass nearly all of the US mobile operating system market (iOS 58% and Android 42% [72]); requiring at least a modest degree of digital literacy; however, most US adults have basic computer skills and can be considered digitally literate (84%) [73] and evidence suggests that individuals with lower digital literacy are interested in and receptive to digital cessation treatments [74]; and requiring users to speak English; however, there are plans to include additional languages. Therefore, we do not anticipate these potential limitations will affect the feasibility or utility of this infrastructure.

### Conclusions

In conclusion, consumers need evidence-based, sustainable, and tailored mHealth interventions, while researchers need feasible, cost-effective, and streamlined infrastructure to support the development of mHealth apps. The mFLi platform has enormous potential to advance public health efforts, as its demonstrated feasibility (via the 3 demonstration projects) would support its use to facilitate the creation, testing, and implementation of a wide variety of mHealth behavioral interventions.

## Appendix

Multimedia Appendix 1 Peer review report by Florida Department of Health Biomedical Research Program.

## Abbreviations

AAC: Ask-Advise-Connect
D-MAPS: Digital Motivation and Problem Solving
EHR: electronic health record
EMA: ecological momentary assessment
HIPAA: Health Insurance Portability and Accountability Act
mFLi: mHealth Florida infrastructure
mHealth: mobile health
QT: quitline treatment
RCT: randomized controlled trial
REDCap: Research Electronic Data Capture
UI: user interface
UX: user experience
